# Laparoscopic sacrocolpopexy versus vaginal sacrospinous fixation for vaginal vault prolapse, a randomized controlled trial: SALTO-2 trial, study protocol

**DOI:** 10.1186/s12905-017-0402-2

**Published:** 2017-07-26

**Keywords:** Laparoscopic sacrocolpopexy, Laparoscopic sacral colpopexy, Pelvic organ prolapse, Vaginal sacrospinous ligament fixation, Vaginal sacrospinous suspension, Vault prolapse

## Abstract

**Background:**

Hysterectomy is one of the most performed surgical procedures during lifetime. Almost 10 % of women who have had a hysterectomy because of prolapse symptoms, will visit a gynaecologist for a surgical correction of a vaginal vault prolapse thereafter. Vaginal vault prolapse can be corrected by many different surgical procedures. A Cochrane review comparing abdominal sacrocolpopexy to vaginal sacrospinous fixation considered the open abdominal procedure as the treatment of first choice for prolapse of the vaginal vault, although operation time and hospital stay is longer. Literature also shows that hospital stay and blood loss are less after a laparoscopic sacrocolpopexy compared to the abdominal technique.

To date, it is unclear which of these techniques leads to the best operative result and the highest patient satisfaction. Prospective trials comparing vaginal sacrospinous fixation and laparoscopic sacrocolpopexy are lacking. The aim of this randomized trial is to compare the disease specific quality of life of the vaginal sacrospinous fixation and laparoscopic sacrocolpopexy as the treatment of vaginal vault prolapse.

**Methods:**

We will perform a multicentre prospective randomized controlled trial. Women with a post-hysterectomy symptomatic, POP-Q stage ≥2, vaginal vault prolapse will be included. Participants will be randomized to the vaginal sacrospinous fixation group or the laparoscopic sacrocolpopexy group.

Primary outcome is disease specific quality of life at 12 months follow-up. Secondary outcome will be the effect of the surgical treatment on prolapse related symptoms, sexual functioning, procedure related morbidity, hospital stay, post-operative recovery, anatomical results using the POP-Q classification after one and 5 years follow-up, type and number of re-interventions, costs and cost-effectiveness. Analysis will be performed according to the intention to treat principle and not as a per protocol analysis. With a power of 90% and a level of 0.05, the calculated sample size necessary is 96 patients. Taking into account 10% attrition, a number of 106 patients (53 in each arm) will be included.

**Discussion:**

The SALTO-2 trial is a randomized controlled multicentre trial to evaluate whether the laparoscopic sacrocolpopexy or vaginal sacrospinous fixation is the first-choice surgical treatment in patients with a stage ≥2 vault prolapse.

**Trial registration:**

Netherlands Trial Register (NTR): NTR3977; Registered 28 April 2013.

## Background

Hysterectomy is one of the most performed surgical procedures during a women’s lifetime. Almost 10% of women who have had a hysterectomy because of prolapse symptoms, will visit a gynaecologist for a surgical correction of a vaginal vault prolapse (VVP) thereafter. VVP can be corrected by many different surgical procedures. These symptoms are directly related to the prolapse and contain of pelvic pressure, bulging of the vaginal wall, dropping sensation in the vagina or backache. Other symptoms that are often present, are symptoms of the bladder, bowel and sexual problems [1]. These symptoms could affect the quality of life of these women severely. Therefore, an effective treatment is required.

The incidence of post-hysterectomy VVP requiring surgical treatment, has been estimated at 36 per 10,000 person-years [2]. The longer the time after hysterectomy, the higher the risk of vault prolapse. If the initial reason for hysterectomy was genital prolapse the risk increases significantly [1–3]. Women tend to get older and older and due to this improved life expectancy, there will be an enormous extra demand for future prolapse surgery.

Surgery for pelvic organ prolapse, including VVP, focuses on the correction of the normal anatomy of the vagina, resulting in normal function of the bladder and bowel. To date, a variety of surgical interventions to treat VVP surgically have been described [4]. These procedures can be performed vaginally or abdominally. The abdominal route can be performed as an open or laparoscopic sacrocolpopexy (LSC). The vaginal approach includes the vaginal sacrospinous fixation (VSF), which was first reported in 1958 [5]. This is probably the most performed treatment modality of VVP at the moment. In a questionnaire of the International Urogynecological Association (IUGA), which was performed in 2002, VSF was the most performed surgical correction for the VVP, as 78% of the responders reported the VSF as the first-choice treatment for VVP [6]. The LSC technique was developed in the footsteps of the abdominal sacrocolpopexy, and has, been implemented since then [7].

No randomized controlled trials comparing VSF and LSC have been performed. A Cochrane review shows that abdominal sacrocolpopexy is better compared to VSF. The recurrence rate of VVP was lower after an abdominal sacrocolpopexy (RR 0.23, 95% CI 0.07 to 0.77) and dyspareunia was less (RR) 0.39, 95% CI 0.18 to 0.86). However, the rates of recurrence surgery for prolapse show no statistical difference (RR 0.46, 95% CI 0.19 to 1.11). The VSF has a shorter operation time, lower costs and an earlier return to daily activities [8]. In none of the included studies disease specific quality of life was the primary outcome. Furthermore, in some of the studies no power analysis was done.

A cohort study comparing laparoscopic to abdominal sacrocolpopexy shows a significant reduction in hospitalization (1.8 ± 1.0 days vs 4.0 ± 1.8 days; *p* < 0 .0001) [9]. A prospective cohort study comparing laparoscopic to abdominal sacrocolpopexy that we performed prior to this study revealed a significant reduction in blood loss (77 ml (±182) versus 192 ml (±126) respectively, p = <.001) and hospital stay (2.4 days versus 4.2 days respectively, p = <.001) and less procedure related morbidity (RR 0.24 (95%-CI 0.07–0.80), *p* = 0.009) [10].

The laparoscopic procedure seems to have advantages over the abdominal procedure.

Since prospective trials comparing VSF and LSC sacrocolpopexy are lacking we plan to perform a RCT. The aim of this randomized trial is to compare the disease specific quality of life of the VSF and LSC as the treatment of VVP.

## Methods/study design

### Study design

The SALTO-2 trial is a randomized controlled multicentre trial and will be performed to compare VSF versus LSC for VVP. The follow-up time will be one and 5 years.

The trial will be a non-blinded trial, since it is impossible to blind the participating women and medical staff for the allocated technique, since one procedure will be performed vaginally and the other one laparoscopically, leaving small abdominal scars. However, a physician blinded for the intervention will perform follow-up examination. This will be another physician than the surgeon who performed the operation. The study design is presented in Fig. 1.

**Fig. 1 Fig1:**
[figure not shown]
Study design

### Objectives

The objective of this study is to determine whether LSC in women with vault prolapse, POP-Q stage 2 or higher, improves outcome in terms of disease specific quality of life, recurrence of prolapse, complications, hospital stay, post-operative recovery, sexual functioning, costs and costs-effectiveness, compared to VSF.

### Hypothesis

Based on the literature, we expect that the LSC will be equally or more successful in correction of vault prolapse and its related disease specific quality of life as compared to VSF.

### Participating hospitals

The trial will be performed in several teaching and academic hospitals in the Netherlands. The nine participating centres are Máxima Medical Centre, Isala Clinics, Spaarne Gasthuis, Catharina Hospital, Maastricht Academic Hospital, Gelre Hospital, Radboud Academic Hospital, Sint Lucas Andreas Hospital, VU Medical Centre and Martini Hospital. Before the start of the trial, a masterclass was organised to reach consensus on the details of operation technique of the LSC and VSF and evaluate the operation skills of the participating surgeons. All participating gynaecologists performed at least 25 procedures before the beginning of the trial to exclude a learning curve.

During this master class, which was attended by many experienced surgeons, several surgical steps of both procedures were discussed (for the sacrocolpopexy: type of mesh, type of sutures, number of sutures, dissection technique, re-peritonealisation, (no) obliteration of Douglas pouch. For the VSF: (no) hydro dissection type and number of sutures, concomitant prolapse surgery). Decisions which techniques should be used were made and recorded to reduce practice variation as much as possible and to carry out a uniform operation technique during the inclusion period.

### Study population and recruitment

All patients with a symptomatic post-hysterectomy VVP stage 2 or higher (according to POP-Q classification) who need surgical treatment are eligible for the study.

#### Inclusion criteria

In order to be eligible to participate in this study, a subject must meet all of the following criteria:Symptomatic vault prolapse POP-Q ≥ stage 2 which needs surgical treatmentEligible for both surgical treatmentsPatients must be able to read Dutch

#### Exclusion criteria

A potential subject who meets any of the following criteria will be excluded from participation in this study:Previous surgical treatment of vault prolapseContra-indication for a surgical interventionIncapacitated patients, illiterate patients or patients with other language barriers

Patients with co-existing anterior/posterior defects or concomitant incontinence surgery can be included. Patients need to agree to return the questionnaires and visit the follow-up appointments.

Patients who don’t want to participate in the trial because of a preference for one of both surgical options will be asked for a cohort group and requested to complete the questionnaires as well. This cohort group will be compared to the study population to analyse whether a patients preference will affect the quality of life.

Assessment for eligibility will be performed by a gynaecologist of the participating hospital. Women eligible for this trial will be counselled for the trial. Subsequently, written patient information is provided, which contains information on the objectives, design, methods, possible advantages and disadvantages of the study treatments, and information that non-co-operation with the study or withdrawal will not have consequences for their treatment. Before randomization, written informed consent will be obtained.

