### Sample size calculation

We will consider the score of the UDI genital prolapse domain as primary endpoint. A difference between both surgical techniques of 10 points on the genital prolapse domain of the UDI 1 year after surgery, will be considered a clinically relevant difference between both groups [19]. The standard deviation of the score on this domain is 15 points [19]. With a power of 90% and a level of 0.05, the calculated sample size necessary is 96 (48 in each group).

The analysis will be performed by intention to treat. Odds ratios and 95% confidence intervals are calculated for all terms that are included in the regression model. Domain scores will be analysed using repeated measurement analysis.

Taking into account 10% attrition, a number of 106 patients (53 in each arm) will be included.

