### Randomization

The trial represents a multi-centre randomized controlled design. Eligible patients with vault prolapse who meet the inclusion criteria will be randomized when informed consent is signed. The treatment allocation ratio is 1:1 to either LSC or VSF. Stratified randomization will be used to achieve approximate balance of participating centres across study groups. The investigators or the participating surgeons are not aware of these series. Randomization will be performed by the coordinating researcher, after which the procedure can be planned. For randomization, opaque sealed envelopes will be used in order to conceal the allocation. To evaluate data anonymously, participants will receive a case number at randomization. Blinding for allocation of treatment is impossible because of the laparoscopic or vaginal approach which requires a different introduction and anaesthesia technique. However, the follow up visit at one and 5 years will be performed by a physician blinded for the intervention.

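### The preference cohort is set against the randomized women without separating the two operations, so an uneven choice of operation could pass for an effect of preference

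*Protocol article*

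**What the plan says.** The cohort is described only in the protocol article, under Exclusion criteria. Women who refuse the trial "because of a preference for one of both surgical options will be asked for a cohort group" and are asked to fill in the same questionnaires. The purpose and the contrast follow in one sentence: "This cohort group will be compared to the study population to analyse whether a patients preference will affect the quality of life".

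The make-up of the other side of that contrast is fixed under Randomization: "The treatment allocation ratio is 1:1 to either LSC or VSF".

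No section splits the cohort comparison by operation or adjusts it for operation. The Data analysis section names stratification by centre and an unpaired t-test for continuous variables, but does not mention the cohort. The comparison is absent from the primary and secondary outcomes and has no sample size.

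**The concern.** The article names two groups and the inference to be drawn from comparing them. The groups differ in how women came to their operation, which is the point of interest, but they may also differ in which operation they had. The randomized group is half LSC and half VSF by design. The cohort's mix is whatever the women choose. If outcomes differ between the operations, part of that difference enters the cohort-versus-trial contrast and is read as an effect of preference. It can create an apparent effect where there is none, or offset a real one.

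The comparison would be unbiased only if the cohort happens to split evenly or the operations have equal outcomes. The second condition is what the trial sets out to test.

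A further difference is that women who refuse randomization may differ from participants at baseline. Comparing within operation does not remove that.

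**Working it through.** **Inputs from the article**
- Randomized mix: 1:1, so a share of 0.5 has LSC (Randomization).
- Planning difference: "A difference between both surgical techniques of 10 points on the genital prolapse domain of the UDI 1 year after surgery" (Sample size calculation).
- Spread: "The standard deviation of the score on this domain is 15 points" (same section).
- Analysed size: "With a power of 90% and a level of 0.05, the calculated sample size necessary is 96 (48 in each group" (same section).

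**Inputs that the article does not give, taken as assumptions**
- q, the share of the cohort having LSC: any value from 0 to 1. The Background cites a survey in which 78% named VSF as first choice, but those were questionnaire responders and not patients choosing for themselves, so it is not used as an estimate of q.
- Cohort size: 50, 96 or 150.
- The outcome: the cohort sentence says quality of life without naming an instrument. The UDI genital prolapse domain is used because it is the only scale with a stated difference and standard deviation.

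**Step 1: the plan's own figure.** Per arm, n = 2 x (1.960 + 1.282)^2 x 15^2 / 10^2 = 2 x 10.51 x 2.25 = 47.3, rounded up to 48, or 96 in total. This matches the article; power at 48 per arm is 90.4% by the normal approximation. Nothing below changes this figure.

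**Step 2: expected contrast with no preference effect.** Let L and V be the mean scores after LSC and VSF, and D = L - V.
- Cohort mean: qL + (1 - q)V
- Randomized mean: 0.5L + 0.5V
- Difference: (q - 0.5) x (L - V) = (q - 0.5) x D

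**Step 3: size.** The table takes D = 10 as planned and D = 5 for comparison. Shares below one half give the mirror image.

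| Cohort share having one operation | D = 10 | D = 5 |
|---|---|---|
| 50% | 0 | 0 |
| 60% | 1 | 0.5 |
| 70% | 2 | 1 |
| 80% | 3 | 1.5 |
| 90% | 4 | 2 |
| 100% | 5 | 2.5 |

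With D = 0 every entry is 0.

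**Step 4: how often a test would be misled.** Take a standard deviation of 15 within each operation, 96 randomized women and m cohort women. The standard error of the unadjusted contrast is the square root of [225 + 100q(1 - q)]/m + [225 + 25]/96. For m = 96 and q = 0.8 this is the square root of 241/96 + 250/96, or 2.26 points, against a spurious difference of 3 points. With D = 10 and no preference effect, a nominal 5% two-sided test rejects as follows.

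| Split | m = 50 | m = 96 | m = 150 |
|---|---|---|---|
| 50% | 5% | 5% | 5% |
| 70% | 11% | 14% | 16% |
| 80% | 20% | 26% | 31% |
| 90% | 32% | 43% | 50% |
| 100% | 47% | 61% | 69% |

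**Step 5: effect of comparing within operation.** Cohort LSC against randomized LSC has expectation L - L = 0 when preference has no effect, and likewise V - V = 0 for VSF. The operation term vanishes for every q and D. Any baseline differences between women who refuse and women who accept randomization remain.

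**The case against.** The strongest reply is that the article does not say the operations are pooled. It gives no test, endpoint, time point or covariates for this comparison, and a within-operation analysis could sit under the same sentence. The full protocol and any analysis plan are not shown, and the model for an ancillary non-randomized comparison is a detail that an article may leave to them. This stands in part. Pooling is the natural reading of one group compared with one population, but it is an inference. The point survives because the article goes beyond silence: it states both the groups and the conclusion to be drawn, and those groups alone do not isolate preference.

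The reply is also right that the size is conditional. The 10 points is the difference judged clinically relevant for the sample size and not an observed one. The Hypothesis section allows that the operations may do equally well, in which case the term is zero whatever the split. Five points needs the full 10-point difference and every cohort woman having the same operation.

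A reader might infer more than the text supports:
- That the preference effect is confounded as a matter of fact. The documents give neither the cohort split nor the true difference between operations.
- That cohort women will be added to the LSC-versus-VSF comparison. Nothing in the article proposes this.
- That baseline differences will be left unadjusted. The article does not say so, and cohort women complete the questionnaires, whose schedule includes baseline.

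**Conclusion.** The point holds in a conditional form. As worded, the preference comparison mixes preference with operation whenever the cohort splits unevenly and the operations differ. The size is (q - 0.5) x D: 1 to 5 points on the UDI genital prolapse domain for splits of 60% to 100% if D is the planned 10 points, half that if D is 5, and zero for an even split or equal operations. The upper end is half the difference that the article calls clinically relevant. The rejection rates also rest on assumed cohort sizes and a normal approximation.

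The comparison is ancillary. The randomized comparison, its sample size and its interpretation are untouched, so this is a low-cost improvement to a side analysis and not a fault in the trial's main result.

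**What to change.** Reword the sentence under Exclusion criteria, or settle it in the analysis plan if that does not already do so:
- Compare cohort and randomized women within each operation, or fit a linear model with terms for operation and source (cohort or randomized).
- Adjust for the baseline UDI score. Adjust for POP-Q stage only if it is recorded for cohort women: it comes from a clinical examination, and the article asks this group only for questionnaires.
- Add an operation-by-source interaction only if both operations are adequately represented in the cohort. If all cohort women have the same operation, it cannot be estimated.
- Name the quality-of-life score and the time point.
- Report the result as a non-randomized association.

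The cost is a few lines of text and one recorded item, the operation of each cohort woman. No change to the randomized design, sample size or primary analysis is needed.

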### Interventions

#### Vaginal sacrospinous fixation

The patient is placed in lithotomy position. The sacrospinous ligament will be accessed through an incision following the length of the posterior vaginal wall, extending up to the vaginal vault. Blunt dissection is used to open the right pararectal space and locate the ischial spine. A ‘window’ is created through the rectal pillar, large enough for two fingers. Just lateral to the rectum and above the puborectal muscle, the right sacrospinous ligament-coccygeus muscle complex will be exposed. Three Breisky specula will be positioned, whereafter two Prolene 1–0 sutures will be placed under direct vision. These two permanent non-absorbable sutures will be put into the sacrospinous ligament at about 0.5 cm apart, with the lateral suture being placed about 2 cm from the ischial spine. The sutures will be attached to the vault on the suture line were the vault was closed after hysterectomy seeking the part with most connective tissue or ligament remains.

#### Laparoscopic sacrocolpopexy

Patients don’t receive bowel preparation the day before the operation. Looking at the design of this surgical intervention, the main goal of sacrocolpopexy is to reconstitute an adequate, durable system of support and suspension of the vagina by replacing the impaired and/or detached native fascial tissue with a synthetic non-absorbable prosthesis. The LSC will be performed under general anaesthesia with four trocars, one for the scope and three side trocars. The vaginal vault will be lifted using a vaginal probe. The peritoneum will be dissected to expose the vesicovaginal and rectovaginal fascia, extending to the sacral promontory. Preparation of the rectovaginal and vesicovaginal fascia will be done as far down as possible. The preparated tissue and the size of the mesh will be measured and documented. One side of the polypropylene mesh will be attached anteriorly of the vaginal wall, and the other side as far down posteriorly as possible using absorbable sutures. As little as possible stitches will be used. Depending on the surgeon’s preference, the mesh will be attached to the sacral promontory using staples or non-absorbable sutures. The mesh will be peritonealised at several points. The pouch of Douglas will not be obliterated.

The VSF can be performed under spinal or general anaesthesia, depending to the patient’s and anaesthesiologist’s preferences. The laparoscopic procedure will be performed under general anaesthesia. Both procedures will be completed with any additional vaginal surgery, if indicated, after the vault suspension has been carried out. For example anterior and posterior colporrhaphy may be performed during the same procedure. No vaginal mesh augmented procedures are allowed.

In both groups, prophylactic antibiotics and thrombosis prophylaxis will be given per-operatively. An indwelling urine catheter will be left in-situ and will be removed the first day post-operatively or as clinically indicated. Prolonged catheterisation will be recorded. If necessary, patients will receive analgesics according to the local hospital protocol. Patients are advised to withhold from heavy physical work for a minimal period of 6 weeks.

In case clinically indicated (complication or technical challenge to continue the procedure), the surgeon could convert to the other intervention. Participants will be analysed according to the intention to treat principle.

